## 5. Conclusions

This pilot study is the first to examine the effect of a CTR intervention on patients with heart failure in a cardiac rehabilitation setting in the Hospital of Melilla (Spain). Efficacy, feasibility, adherence, satisfaction, and cost-effectiveness must show if this study will add more evidence in support of the use of CTR program as an effective tool in new cardiac rehabilitation programs.

## Figures and Tables

**Figure 1 ijerph-18-04038-f001:**
[figure not shown]
Study design. Abbreviations CVD, cardiovascular disease; CTR, cardio-telerehabilitation.

**Table 1 ijerph-18-04038-t001:** Inclusion and exclusion criteria.

Inclusions Criteria	Exclusions Criteria
Adult over 18 Years old	Cognitive ability not suitable for the use of technologic tools.
Diagnosis: Ischemic heart disease in New York Heart Association (NYHA) functional class I-II with preserved global systolic function or in intermediate range (LVEF > 40%) after revascularized acute coronary syndrome.	
Lives in Melilla during the research period.	Absolute or relative contraindications to exercise testing
To have mobile technology with an internet connection at home (including one of the following devices: desktop personal computer, laptop, tablet, or smartphone)	
Ability and knowledge to access email or instant messaging	

Abbreviations LVEF, Left ventricular ejection Fraction.

**Table 2 ijerph-18-04038-t002:** Primary and secondary outcomes.

	Definition	Type
Primary Outcomes		
Biochemical	Hematies Level, Glucose, Creatine Kinase (CK), Triglycerides, Total Cholesterol, High Density Lipoprotein Cholesterol (HDL-C), Low Density Lipoprotein Cholesterol (LDL-C), Glycated Hemoglobin (HbA1c)	Clinical
Cardiac Function	Metabolic Equivalent (MET), Resting Heart Rate (RHR), Maximum Heart Rate (HRmax), Final Heart Rate (FHR), Rating Scale for Perceived Exertion (RPE), Systolic Blood Pressure (SBP), Diastolic Blood Pressure (DBP)	Clinical
Quality of Life	SF-12, EQ-5D	Self-Reported
Functional Capacity	Duke Activity Status Index (DASI)	Self-Reported
Secondary Outcomes		
Feasibility, Satisfaction and Usefulness	Telemedicine Satisfaction and usefulness Questionaire (TSUQ)	Self-Reported
Cost-Effectiveness	Direct Costs/Indirect Costs	€/Self-Reported
Adherence and Safety	Nº of sessions completed and adverse events record	Automatized App record

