## 2. Material and Methods

This piece of research is a single center prospective controlled trial conducted at the Regional Hospital of Melilla (Spain), which will facilitate voluntary participant recruitment and the supervised CTR program component.

This research involves the departments of Cardiology, Rehabilitation, Physiotherapy, and Research at the University of Granada. All CTR staff will receive training on how to integrate the intervention training. As this study runs parallel to clinical practice, all medical management, including medication prescription, will be at the discretion of the treating physician. All changes will be documented and considered during analysis. 

This research uses the guidelines on Standards for Quality Improvement and Excellence in Reporting (SQUIRE) [18] and will be carried out in accordance with CONSORT (Consolidated Standards of Reporting Trials) criteria [19]. A Standard Protocol Items Recommendations for Interventional Trials (SPIRIT) checklist is provided as Supplementary File S1, and the flow diagram for the study protocols is included as Figure 1.

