### 2.1. Patients

The trial includes adults with a diagnosis of low-risk CVD with class I heart failure according to the NYHA (New York Heart Association) functional assessment criteria (24), diagnosed by the Cardiology and Rehabilitation team of the Hospital of Melilla. Patients must live in Melilla during the intervention phase, have mobile technology with an internet connection at home (including one of the following devices: desktop personal computer, laptop, tablet, or smartphone), and be able to access email or instant messaging frequently and reliably. Patients who suffered non-mild cardiac events prior to the first contact with this research, those whose pathologies are not classified as CVD, and those subjects who are not in full cognitive capacity that allows them to use new technology tools will be excluded. Patients will be excluded if they have any absolute or relative contraindications to exercise testing as per the American Heart Association guidelines [20]. Inclusion and exclusion criteria is show in Table 1.

In order to generate sufficient data for the development of this research, a sample size of (*n* = 30) patients will be recruited. The primary aims of this sample size determination is to evaluate whether the proposed intervention is feasible, safe, and effective. A larger randomized controlled trial that would have adequate power could be designed based on what was learned in this study. The strategies to achieve an adequate inclusion of participants that reach the target sample size include the multidisciplinary collaboration of the team from the Regional Hospital of Melilla (Cardiology Department, Head of the Rehabilitation Service and the Physiotherapy team). The collaborators were informed about the characteristics of the study in personal interviews and presentation. We ensured that the recruitment of patients has a socio-demographic diversity in relation to their social origin, gender, ethnicity, and education adapted to the particularities of the reference population. For the development of this research, an intentional non-probabilistic type of sampling will be used for the convenience of the study, due to the characteristics of the subjects. This trial has the approval of the Andalucía Ethics Committee with HIP version 17112020.

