### 2.2. Intervention

Participants are assigned to the cardiac telerehabilitation group to receive an initial assessment. The CTR group receives a personalized 8-week exercise program through a mHealth application that allows health professionals to generate videos, images, and parameters of each exercise, as well as send them by email, instant messaging, and follow up on patients. In this study, we use the Physiotec exercise prescription app as it allows us to create personalized CTR programs according to particular clinical case and follow their progress. The CTR program describes the exercises to be performed, the number of repetitions according to the level of training and the criteria for progression. The CTR program includes aerobic exercise at 60–85% of the maximum heart rate (HR) reached in the ergometry test. As patients are taking β-blocker drugs, they will never reach their maximum HR. Patients will be instructed in the use of the Modified Borg Scale to assess their level of fatigue while performing the CTR program. Exercises customized to each participant should be performed between values 4–6 on this scale (out of a maximum of 10).

The type of exercise can be continuous or intervallic (load or HR controlled):

Continuous Exercise: After an initial warm-up period of 5–10 min, the patient is brought into a phase where he or she remains at a HR or resistance previously determined by the intervention team.

Interval Exercise: After an initial warm-up period, an exercise is started which alternates load peaks with lower intensity ones.

All patient training sessions should end with a return to the initial baseline situation (relaxation phase) of similar duration to the warm-up phase 5–10 min.

Typical CTR training session: -Control of basal constants (by the patient): HR, blood pressure, weight, blood sugar…-Permanent monitoring during the whole CTR session (patient must understand and follow the modified Borg scale as well as to use activity bracelets, pulse meters, or other monitoring instruments)-Exercise session:
∘Initial warm-up: 5–10 min (follow-up the video exercises provided through the CTR tool).∘Aerobic training: 35–45 min (follow up the video exercises provided through the CTR tool)∘Return to calm, relaxation-cooling: 5–10 min (follow up of the video exercises provided through the CTR tool)∘Recording of incidents and patient feedback in the CTR tool. Patient/physiotherapist feedback

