#### 2.3.1. Main Explanatory Variable

-Biochemical outcomes: obtained by blood analysis performed at the Hospital of Melilla including the following measures: red blood cell levels, glucose, creatine kinase (CK), triglycerides, cholesterol, high-density lipoprotein cholesterol (HDL-C), low-density cholesterol (LDL-C), and glycosylated hemoglobin (HbA1c).-Cardiac function: obtained by performing an ergometry test at the Hospital of Melilla, including the following measurements: metabolic equivalent (MET), resting heart rate (HRrest), maximum heart rate (HRmax), and final heart rate (HRfinal), rating of perception of exertion scale (RPE), systolic blood pressure (SBP), diastolic blood pressure (DBP).-Quality of life: obtained through the completion of self-reported questionnaires with the advice of the research team. The assessment of health-related quality of life will be assessed by the following two questionnaires: SF-12 and EuroQoL-5d. The SF-12 questionnaire is the short version of the SF-36, containing twelve questions from the SF-36. [21]. The SF-12 is an appropriate instrument of choice and is a practical alternative for measuring the general health status of the population [22]. The SF-12 questionnaire assesses eight dimensions of health-related quality of life: physical function, physical role, bodily pain, general health, vitality, social function, emotional role, and mental health [21]. Two sum scores are also obtained for the physical health component and the mental health component of the person. Thus, the sum index of the physical and mental component corresponds to the overall idea of general health. The EuroQoL-5D Questionnaire (EQ-5D) contains a descriptive system of one’s health status measured in five dimensions (mobility, self-care, activities of daily living, pain, and anxiety/depression) [23]. The EQ-5D has a visual analog scale (VAS) that assesses health status “on the present day” with scores ranging from 0 (worst imaginable health status) to 100 (best imaginable health status). The EQ-5D questionnaire provides information on the level of the problem (no problem, somewhat/moderate problem or severe problem) [24]. It has been shown to be a tool with an acceptable validity, with an estimated mean of 0.87 [25].-Functional capacity: For the assessment of functional capacity we will use the Duke Activity Status Index (DASI). It is an assessment tool used to evaluate the functional capacity of patients with cardiovascular disease, such as coronary artery disease, myocardial infarction, and heart failure. It is a validated instrument and its Spanish version is available [26,27]. The original version include 12 questions on aspects of physical function related to activities of daily living. It allows a calculation of functional capacity reporting results in ml of O2/kg/minute with good correlation with peak VO2, and in turn can be compared with the METs [28].

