### 2.5. Statistical Analysis

This research is a single center prospective controlled trial pre/post design. The results of the trial research will be presented as a summary of the outcome measures, together with the estimated effect size and precision. Statistical analysis will be performed according to the intention-to-treat principle. Patient characteristics will be summarized using frequencies and percentages for categorical factors, and using means and standard deviations for continuous measures in order to have as much information as possible available for exploration and analysis. The effect sizes will be calculated using Cohen’s d, so that the results can be compared to other studies. The outcome measures will be compared before and after the completion of the 8-week CTR program. All statistical analyses will be conducted using SPSS software. Statistical significance was set at *p* < 0.05.

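### Eligibility sets no interval from the qualifying coronary event to T0, so the one-group pre/post change cannot separate recovery from the effect of CTR

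*Protocol article*

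**What the plan says.** **Entry.** Table 1 requires ischaemic heart disease in NYHA class I-II, "with preserved global systolic function or in intermediate range (LVEF > 40%) after revascularized acute coronary syndrome". No earliest or latest time from the event to T0 is given, and no condition on settled drug treatment. Section 2.1 adds neither. It describes low-risk patients in NYHA class I and excludes "Patients who suffered non-mild cardiac events prior to the first contact with this research", again without a time limit. The only other criterion that might screen for stability is the exclusion for "Absolute or relative contraindications to exercise testing", which Section 2.1 ties to a cited guideline.

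**Treatment.** Section 2 says that "all medical management, including medication prescription, will be at the discretion of the treating physician", and then that "All changes will be documented and considered during analysis". Section 2.2 takes it as given that participants use β-blockers ("As patients are taking β-blocker drugs, they will never reach their maximum HR"), but no criterion requires this or a settled dose.

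**Outcomes and analysis.** The primary outcomes include eight blood measures, among them "red blood cell levels, glucose, creatine kinase (CK), triglycerides, cholesterol", and seven ergometry measures, three of which are heart rates. Section 2.2 assigns participants to the CTR group and describes no other. Section 2.5 names a pre/post design and states: "The outcome measures will be compared before and after the completion of the 8-week CTR program". The Results section says that beneficial effects would prove the effectiveness of the intervention.

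**The concern.** In a one-group pre/post comparison, any change that would have happened without the program becomes part of the estimated effect. After a revascularised acute coronary syndrome, such change is plausible in many of the 15 biochemical and ergometry measures, and how much of it remains at T0 depends on how long ago the event was. A drug started shortly before T0, with its effect showing by T1, acts the same way. Table 1 leaves that interval open.

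Two things are at stake. An ineffective program could yield significant improvements that the article says it would read as proof. In addition, the Cohen's d values promised in Section 2.5 could be too large, and Section 2.1 says that a larger randomised trial could be designed from what is learned here.

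**Working it through.** The article gives 30 as a recruitment target with no effect size, SD or power behind it, so there is no figure to reproduce. The check has two parts.

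**1. Which source of change does the text deal with?**

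| Source of T0-T1 change | Text that bears on it | Separated from CTR? |
|---|---|---|
| Recovery after the index event | None found | No |
| Drug started shortly before T0, effect appearing by T1 | No stable-treatment condition; Section 2 read as covering changes during the study does not reach it | No |
| Drug changed between T0 and T1 | Section 2: documented and taken into account in the analysis | In principle; method not shown |
| Any change shared with untreated patients | No comparator described | No |

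**2. How much drift is enough to mislead?** The document gives no drift size, so a range is assumed.

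Inputs:
- n = 30 (Sections 2.1 and 3).
- Significance level 0.05 (Section 2.5); two-sided is assumed, because the article does not say.
- A paired t-test is assumed for the pre/post comparison.
- True effect of CTR = 0.
- d = background mean change divided by the SD of the paired change (assumed).

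Formulas: df = 30 − 1 = 29; critical t = 2.045; noncentrality = d × √30 = d × 5.477. The chance of a significant result in the favourable direction is P(T > 2.045), where T is noncentral t with 29 df.

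| Assumed drift d | Noncentrality | Chance of a significant improvement, one measure |
|---|---|---|
| 0 | 0 | 2.5% |
| 0.1 | 0.548 | 7.6% |
| 0.2 | 1.095 | 18.4% |
| 0.3 | 1.643 | 35.5% |
| 0.4 | 2.191 | 56.3% |
| 0.5 | 2.739 | 75.4% |

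The observed mean change that just reaches p = 0.05 is 2.045 / 5.477 = 0.37 SD.

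**Mixed sample.** Suppose half the patients are recent cases with a drift of 0.5 SD and half are remote cases with none. The mean drift is 0.5 × 0.5 = 0.25. The mixture adds variance 0.5 × 0.5 × 0.5² = 0.0625, so the SD rises to √1.0625 = 1.031 and d = 0.25 / 1.031 = 0.243. Noncentrality is 0.243 × 5.477 = 1.33, and the chance is about 25%.

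The comparison value throughout is 2.5%, because only improvement is counted. The two-sided 5% includes significant worsening.

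**The case against.** Several points on the other side have force.

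- **Drug changes are addressed.** A reader might infer that drug titration during the study will simply be counted as benefit of CTR. The text does not support that: Section 2 commits to documenting changes and taking them into account, and the method may properly sit in an analysis plan not shown. This stands. What remains is recovery, and drugs started before T0.
- **Very recent cases may be barred.** A reader might infer that patients can enter days after the event. The low-risk description, the exclusion of non-mild events and the exercise-test exclusion may prevent this. The cited guideline is not in the document, so the question cannot be settled. This stands against the extreme case, but none of these criteria states an interval.
- **Not every measure would drift towards benefit.** The article gives no favourable direction for red cells, HRmax or HRfinal, and more β-blockade need not look like improvement in HRmax. This stands. The illustration is for one measure that does drift favourably, not a count over all 15.
- **The root problem is the missing comparator.** This also stands. An entry window would reduce the bias, not remove it. But the lack of a comparator is exactly why the open interval matters, since concurrent randomised arms would be expected to share the drift.
- **It is a pilot, reported in a condensed article.** Sections 2.1 and 4 defer adequate power and comparison groups to later trials, and a fuller protocol might hold a time window. However, Table 1 is presented as the entry criteria, and the claim of proof is in the article itself.

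**Conclusion.** The point holds in a limited form. As written, recovery after the index event, and the effect of drugs begun shortly before T0, cannot be told apart from an effect of CTR, and the Results section draws a conclusion that the design cannot support.

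The size of the bias is unknown. The range of about 8% to 75% rests on assumed drifts of 0.1 to 0.5 SD, a paired t-test, two-sided 0.05, all 30 patients analysed and no CTR effect. It shows that modest drift would be enough to mislead, not that such drift will occur. A reader might take one of these figures as the trial's actual error rate, and the documents do not support that. Nor can they support a contrast between sites recruiting recent and remote cases, because this is a single-centre trial.

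There is also a plain inconsistency. Section 2.1 excludes non-mild prior events and names NYHA class I, while Table 1 requires a revascularised acute coronary syndrome and allows class I-II. Until these are reconciled, it is unclear who is eligible and how recent an event may be.

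**What to change.** 1. Record the date of the index event, and the doses of drugs bearing on heart rate, blood pressure, lipids and glucose at T0 and T1.
2. Report biochemical and ergometry changes descriptively by time since event, or with it as a covariate, and separately for patients with no relevant drug change.
3. Do not count a change in CK as benefit of CTR where the T0 sample falls in the post-event period, which cardiology should define beforehand.
4. In the Results section, replace the claim of proof with a statement that a pre/post change in one group cannot be attributed to CTR alone.
5. Reconcile Section 2.1 with Table 1 on prior events and NYHA class.

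Whether to set an entry window or a stable-treatment condition is left to the investigators. With enrolment under way since February 2021, it would affect recruitment and the timing of patients' rehabilitation.

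The cost is a few data fields that should be obtainable from clinical records, one additional table and some rewording. The downside is that subgroups of 30 patients are small, so the split is descriptive only and should carry no significance tests.

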## Data Availability

The researcher declares that he follows the protocols of his work regarding the publication of data in accordance with the provisions of Organic Law 15/1999, of 13 December, on the Protection of Personal Data (LOPD), and that the data will be incorporated into a file for the purpose of carrying out this research project. Participating subjects will be informed of the possibility of exercising their rights of access, rectification, cancellation, and opposition of their data at the e-mail address provided by the principal investigator.
